## Abstract

**Background:**

Walking ability is a priority for many children with cerebral palsy (CP) and their parents when considering domains of importance regarding treatment interventions. Partial body-weight supported treadmill training has become an established therapeutic treatment approach to address this demand. Further, new robotic rehabilitation technologies have increasingly been implemented in the clinical setting to allow for longer training sessions with increased step repetitions while maintaining a consistent movement pattern. But the current evidence about its clinical effectiveness in pediatric rehabilitation is weak. The aim of this research project is therefore to investigate the effectiveness of robot-assisted gait training on improvements of functional gait parameters in children with cerebral palsy.

**Methods/Design:**

Children aged 6 to 18 years with bilateral spastic cerebral palsy who are able to walk at least 14 m with or without walking aids will be recruited in two pediatric therapy centers in Switzerland. Within a pragmatic cross-over design with randomized treatment sequences, they perform 5 weeks of robot-assisted gait training (three times per week with a maximum of 45 min walking time each) or a 5-week period of standard treatment, which is individually customized to the needs of the child and usually consists of 1–2 sessions of physiotherapy per week and additional hippotherapy, circuit training as well as occupational therapy as necessary. Both interventions take place in an outpatient setting. The percentage score of the dimension E of the Gross Motor Function Measure-88 (GMFM-88) as primary outcome as well as the dimension D of the GMFM-88, 6-minute and 10-meter walking tests as secondary outcomes are assessed before and at the end of each intervention period. Additionally, a 5-week follow-up assessment is scheduled for the children who are assigned to the standard treatment first. Treatment effects, period effects as well as follow-up effects are analyzed with paired analyses and independent test statistics are used to assess carry-over effects.

**Discussion:**

Although robot-assisted gait training has become an established treatment option to address gait impairments, evidence for its effectiveness is vague. This pragmatic trial will provide important information on its effects under clinical outpatient conditions.

**Trial registration:**

ClinicalTrials.gov: NCT00887848. Registered 23 April 2009.

## Background

Mobility in general as well as the ability to walk is a priority for many children with cerebral palsy (CP) and their parents when considering domains of importance regarding treatment interventions [1]. Parents of children with CP value walking, especially ‘correct’ walking, as a key component of their children’s present and future well-being [2]. Children with poorer walking abilities report a reduced physical well-being [3]. Accordingly, acquiring, retaining or improving gait function in these children is often a main goal of the families and the rehabilitation team.

As training intensity, frequency, specificity and level of repetition with variation play a crucial role in promoting sensomotor learning in patients with disorders of the central nervous system, partial body-weight supported treadmill training (PBWSTT) has become an established therapeutic treatment approach [4–6]. Although two or even three therapists may be needed in severely affected patients to support the movement of the legs and stabilize the pelvis and the trunk, PBWSTT takes an important role in gait rehabilitation of adult patients with a diagnosis of stroke, incomplete spinal cord injury (iSCI), Parkinson’s disease (PD) or multiple sclerosis (MS) [7–11]. There is also an increasing body of evidence that PBWSTT improves walking ability, speed and endurance in children, with most evidence being available for children with mild to moderate cerebral palsy [12–15].

To allow for longer training sessions with more repetitions while maintaining a consistent movement pattern and reducing the burden of the therapists, new robotic rehabilitation technologies have emerged during the last 15 years and have increasingly been implemented in the clinical setting [16]. With the addition of virtual reality (VR) scenarios, especially game-based VR, this type of training further offers the patients diversification, fun and challenge [17]. One domain of rehabilitation robots involves driven gait orthoses (DGO) for robot-assisted gait training (RAGT), which have been originally developed for adults and subsequently adapted for children [18–20]. One of these DGOs is the Lokomat (Hocoma AG, Volketswil, Switzerland, Fig. 1), which, by using the pediatric version, allows a training for children starting at an age of approximately 4 years.

**Fig. 1 Fig1:**
[figure not shown]
Pediatric robot-assisted gait training with the Lokomat. The Lokomat automates gait therapy on a treadmill by two actuated leg orthoses, which can be individually adapted to the patient’s legs and attached with three cuffs, while the patient is secured by means of a counter system with a harness providing partial body-weight support

RAGT with the Lokomat appears to be effective in improving walking abilities in adult patients with stroke or iSCI [21–23]. A systematic review confirmed these results and showed limited evidence in patients with MS, traumatic brain injury (TBI) or PD [16].

In the last years, RAGT has also been tested and implemented in the pediatric neurorehabilitation setting and has been found to be a feasible and safe therapeutic option [20, 24]. However, the current evidence about the clinical effectiveness of RAGT in pediatric populations is weak. Most published results derive from uncontrolled single case studies or case series [20, 25–28] and the few published controlled trials [29, 30] provide inconclusive results so far.

The aim of this research project is therefore to investigate the effectiveness of RAGT on improvements of functional gait parameters in ambulatory children with cerebral palsy in a pragmatic, randomized cross-over trial.

Our hypothesis is that a 5-week phase of RAGT on the Lokomat in an outpatient setting is superior with regard to the improvement in gait function measured with the dimension E of the Gross Motor Function Measure-88 (GMFM-88) compared to a 5-week phase of standard treatment encompassing conventional physiotherapy lessons in children with spastic CP within a cross-over design with a randomized treatment sequence.

## Methods/Design

The design of the study was developed in accordance with the current (2013) version of the Declaration of Helsinki [31] and the extensions of the CONSORT (Consolidated Standards of Reporting Trials) statement for nonpharmacologic treatment interventions [32] as well as for pragmatic trials [33].

Written informed consent and assent is obtained from all the legal guardians and the child by the PI prior to participation.

### Design and setting

This study is designed as a bicenter, single-blinded, pragmatic, randomized cross-over trial. It is carried out in the outpatient setting of the rehabilitation center of the Children’s University Hospital Zurich in Affoltern am Albis and the Pediatric Therapy Center of the Reha Rheinfelden (Switzerland). Children are randomized to two different pre-specified sequences of interventions. The two interventions are RAGT (T) and usual care (C). A child can be randomized to a T/C sequence (TC-group) or to a C/T/C sequence (CTC-group).

The duration of study participation varies dependent on group allocation (Fig. 2): Children allocated to the TC-group start with a first assessment, followed by a 5-week period of RAGT (T-sequence), a subsequent second assessment, a 5-week period of usual care (C-sequence) and a third assessment. Individual study participation will accordingly last 11 weeks for children in the TC-group with three assessment time points.

**Fig. 2 Fig2:**
[figure not shown]
Overview of the outcome measures and the measurement time points per group. Abbreviations: RAGT: Robot-assisted gait training; GMFM-88: Gross Motor Function Measure-88; 10MWT: 10-m walking test; *on an optional basis

In contrast to that, children allocated to the CTC-group start with an assessment followed by 5 weeks of usual care (C-sequence) and a subsequent second assessment. This is succeeded by a 5-week period of RAGT (T-sequence), a third assessment, another 5-week period of usual care (C-sequence) and a follow-up assessment. Thus, study participation for children assigned to the CTC-group lasts 16 weeks. The rationale for the differences in study duration and number of assessments between the study groups is that we want to reduce the burden for the children and their families as much as possible while still gaining information on the preservation of a potential effect at follow-up.

### Eligibility criteria

Children aged 6 to 18 years with the diagnosis of a bilateral di- or quadriplegic spastic CP and a Gross Motor Function Classification System (GMFCS) level II-IV, who are able to walk at least 14 meters with or without walking aids, are eligible for study participation. Although we are aware that these criteria encompass a wide range of different motor abilities and developmental states, we consider it important that our study population represents the whole range we encounter in clinical practice. Further, they have to be able to follow instructions and communicate pain or discomfort.

Exclusion criteria are neurosurgery or orthopedic surgery on the lower extremity or trunk within the last 6 months, having participated in another Lokomat training regime within the previous 6 months as well as a change in concomitant treatment within the last 4 weeks before or during the study period. This holds true for all contraindications outlined in the Lokomat manufacturer’s manual, as for example severe contractures (i.e. > 20° knee extension deficit, >40° hip extension deficit), bone fractures, open skin lesions or circulatory problems. Further criteria and their clinical implementation are described in a recently published paper by a Lokomat expert panel [34].

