### Randomization, allocation concealment, and blinding

Randomization into the two groups with different intervention sequences is performed using a minimization method with a random factor of 0.9, including the factors severity of impairment (GMFCS-level II or III/IV), age (6–11 years or 11–18 years) and Botulinum Toxin A-treatment (present or absent) in the preceding 6 months. Minimization facilitates balancing even small groups in terms of selected patient factors at all stages of a trial. To ensure that group allocation is concealed for patients and their families as well as everyone who is involved at any stage of the trial, the randomization list is generated by a person not belonging to the study team on www.randomizer.at and stored off site. Directly after inclusion of the patient the principal investigator (PI) seeks information about group allocation through a phone call or an e-mail. As soon as a child is allocated to one of the two groups, the assessments and trainings are planned according to the assigned intervention sequence, taking into account as much as possible the families’ requests and the school schedule of the child.

The rater of the primary outcome and parts of the secondary outcomes is blinded as the performance of the child in these tests is video recorded and scored by means of these videos with the rater being unaware of the date the video has been recorded. The same applies to the statistician.

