### Intervention

#### RAGT (T-sequence)

Protocols for PBWSTT as well as RAGT in children are very heterogeneous so far. Session frequencies range from 2 to 5 times per week, session durations vary with most studies reporting 20 to 30 min of treadmill walking per session, and length of treatment varies from 2 weeks to 5 months [34]. As our training protocol prescribes the Lokomat training on an outpatient basis, we consider a session frequency of three times per week with a maximum of 45 min of effective walking time on the Lokomat as feasible and a treatment duration of 5 weeks as clinically adequate.

Trained and experienced therapists, who are used to working with children, perform the Lokomat trainings. The trainings are executed following recently published recommendations [34]. Virtual reality scenarios and other available motivating strategies are used in order to increase the child’s adherence to the training. Body-weight support, gait speed as well as guidance force of the Lokomat are individually adjusted according to the child’s abilities and modified within training sessions and during the course over time. To ensure that uniform standards are applied in both centers, a joint practical training session has been performed and the clinical training standards have been discussed beforehand.

Standard therapies can be continued during the intervention period, but should not include specific walking training and not be changed in frequency. Parents list the type as well as the dosage of concomitant therapy in a personal logbook.

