### Statistical analysis

All data are electronically filed by the PI using EpiData software with double data entry and range checks for data values (EpiData Association, Odense, Denmark). The statistical analyses are carried out with SPSS24 (IBM Corporation, New York, USA) and datasets of all study participants are analyzed on an intention-to-treat basis. Descriptive parameters of the participants will be presented. Treatment effects, period effects as well as follow-up effects of the two different treatment interventions are analyzed with paired *t*-tests or Wilcoxon signed-rank tests for paired samples, with the treatment effect being our primary end-point. Unpaired two-sample *t*-tests or Wilcoxon rank sum tests for unpaired samples are used to determine whether carry-over effects are present [44]. Ninety-five percent confidence intervals are presented with a two-tailed level of significance set at *p* < 0.05. The applied analyses are schematically listed in Fig. 3.

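### An exclusion criterion that reaches into the study period can be met after randomization and is not reconciled with the intention-to-treat analysis of all participants

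*Protocol article*

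**What the plan says.** All references are to the protocol article.

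- **Eligibility criteria.** The sentence that begins "Exclusion criteria are neurosurgery or orthopedic surgery on the lower extremity or trunk within the last 6 months" goes on to list "as well as a change in concomitant treatment within the last 4 weeks before or during the study period". The clause therefore stands as an exclusion criterion. It is not described as a protocol deviation.
- **Randomization, allocation concealment, and blinding.** "Directly after inclusion of the patient the principal investigator (PI) seeks information about group allocation". The study period therefore lies after allocation.
- **Intervention, RAGT (T-sequence).** Standard therapies may continue during robot-assisted training but "should not include specific walking training and not be changed in frequency". No consequence is given if they do change. "Parents list the type as well as the dosage of concomitant therapy in a personal logbook". The usual-care section has parents keep the same kind of record.
- **Design and setting.** "Individual study participation will accordingly last 11 weeks for children in the TC-group", whereas "study participation for children assigned to the CTC-group lasts 16 weeks".
- **Statistical analysis.** "datasets of all study participants are analyzed on an intention-to-treat basis". Missing data are to be multiply imputed, and a subgroup analysis compares children who complete at least 12 training sessions with those who complete fewer.

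**The concern.** An eligibility criterion should be decidable before randomization. Half of this one rests on something that happens afterwards. If staff apply it as written, randomized children leave the trial. If everyone randomized is analysed, that half of the criterion has no effect on the analysis. The article does not say which is meant.

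The event may also be informative. The trial is single-blinded: the video rater and the statistician are masked, but families know which treatment is under way and keep the record that reveals a change. A change in other therapy could plausibly follow from the training load or from how the child is doing, although the article offers no evidence that it does. In addition, the comparator is itself individually tailored therapy, so an adjustment during a usual-care period may be ordinary usual care and yet meet an exclusion criterion.

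What is at stake is who enters the primary comparison in a trial of 34 children, and whether that is settled before or after outcomes have begun to accrue.

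**Working it through.** **1. The passages side by side.** Inclusion comes first, allocation directly after it, and the study period after that. A change during the study period is thus observed after allocation. Two narrower readings would remove the conflict: (a) only changes already planned at enrolment count; (b) the child stops training but the data stay in the analysis. Neither is written. The RAGT section asks for stable therapy frequency without naming a consequence, so the only consequence stated anywhere is exclusion. The imputation sentence is not linked to such children.

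**2. Time at risk.** 11 weeks in TC and 16 in CTC: 16 − 11 = 5 weeks more, and 16/11 = 1.45, or about 45% longer. The extra five weeks are the CTC follow-up period. A CTC child could therefore meet the criterion after both treatment periods, and all measurements for the treatment contrast, are complete.

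**3. The plan's own sample size, for scale.** Inputs from Sample size and power calculation: difference 3.7 percentage points, SD 6.8, power 80%, significance level 5% (two-sided per Statistical analysis). The article does not say which SD this is; I take it as the SD of the within-child difference.
- Normal approximation: (6.8 × (1.960 + 0.842) / 3.7)² = 26.5, so 27.
- Noncentral t with n − 2 degrees of freedom: power 0.79 at n = 28 and 0.81 at n = 29. Rounding up to equal sequences gives 30, with power 0.82.
- Dropout: 30/(1 − 0.10) = 33.3, so 34.

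The stated 30 and 34 reproduce and are not in dispute.

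**4. What further exclusions would do to power.** The article gives no rate, so the rates below are assumptions. They apply on top of 10% dropout from 34.

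| Further exclusions (assumed) | Children left | Power | Enrolment needed for 30 |
|---|---|---|---|
| 0% | 34 × 0.9 = 30.6, so 30 | 0.82 | 34 |
| 10% | 30.6 × 0.9 = 27.5, so 27 | 0.78 | 30/0.81, so 38 |
| 20% | 30.6 × 0.8 = 24.5, so 24 | 0.72 | 30/0.72, so 42 |
| 30% | 30.6 × 0.7 = 21.4, so 21 | 0.66 | 30/0.63, so 48 |

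**5. What they could do to the estimate.** If all N children average m and k removed children average r, the rest average (N·m − k·r)/(N − k). Take N = 34, m = 3.7 and k = 3, all for illustration; N·m = 125.8.
- r = 0: 125.8/31 = 4.06 (up 10%).
- r = −5: (125.8 + 15)/31 = 4.54 (up 23%).
- r = 7.4, twice the mean: (125.8 − 22.2)/31 = 3.34 (down 10%).

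The sign depends wholly on r. The case r = −5 is extreme: under the same SD assumption the standard error of a mean of three is 6.8/√3 = 3.9, and −5 lies 8.7 points, about 2.2 standard errors, below 3.7.

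**The case against.** The Eligibility section says nothing about deleting data or withdrawing children. The only statement of an analysis population is the intention-to-treat sentence, and it is unambiguous. Other text leans towards retention: children with fewer than 12 sessions stay in the dataset for a subgroup analysis, missing values are imputed, and the logbook documents therapy changes. The request for stable therapy frequency suits a screening reading, under which a family expecting a change is not enrolled.

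Much of this stands. A reader might infer that the plan discards randomized children's data, that the effect is thereby inflated, or that the four-child margin (34 − 30) is used up. The documents support none of these:
- No deletion is stated.
- No rate of therapy changes and no outcome for affected children is given. Direction is open as well: therapy intensified during usual care would tend to shrink a child's RAGT-minus-control difference, and therapy intensified during RAGT would tend to enlarge it.
- The margin suffers only if such exclusions occur beyond the predicted 10% dropout.

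What the objection does not remove is that the clause, read literally, reaches past randomization and that neither benign reading is written. Two centers could apply it differently, and the choice could be made once a child's course is known.

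**Conclusion.** The point holds as a badly fixed rule: one clause of the exclusion criteria extends past randomization and is not reconciled with an intention-to-treat analysis of all participants. It rests on the literal wording and on allocation following directly on inclusion. The size and direction of any bias cannot be derived from the article; the power and effect figures above are illustrations under assumed rates and means. The stated sample size is unaffected unless such exclusions are really made. It should be fixed, because the rule bears on who enters the primary analysis of a small trial. Confidence is moderate, because a benign intention is possible.

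**What to change.** Reconcile the Eligibility criteria, RAGT (T-sequence) and Statistical analysis sections:

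- Limit the eligibility criterion to what is known before randomization: a change in the preceding 4 weeks, or one already planned at enrolment.
- Record later changes from the existing parent logbook as protocol deviations.
- Continue the scheduled assessments where possible, and keep these children in the intention-to-treat analysis as randomized.
- If wanted, exclude them only in a per-protocol sensitivity analysis labelled as such.

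Whether study training continues after such a change is a clinical matter and is not addressed here.

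The cost is a few sentences and no new data collection. The small downside is some dilution of the contrast by co-intervention changes, which the sensitivity analysis would help to gauge.

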### Recruitment

Patients are recruited by announcement in schools for children with special needs, in pediatric clinics and in outpatient pediatric physical therapy practices. Additionally, we will inform parents of children who have previously trained on the Lokomat and who fulfill the inclusion criteria about the study in a letter. Information about the study is also made available on the website of the two participating centers as well as of the association of Swiss pediatric physiotherapists. Families interested in participating can then take the initiative and contact one of the two rehabilitation centers.

### Randomization, allocation concealment, and blinding

Randomization into the two groups with different intervention sequences is performed using a minimization method with a random factor of 0.9, including the factors severity of impairment (GMFCS-level II or III/IV), age (6–11 years or 11–18 years) and Botulinum Toxin A-treatment (present or absent) in the preceding 6 months. Minimization facilitates balancing even small groups in terms of selected patient factors at all stages of a trial. To ensure that group allocation is concealed for patients and their families as well as everyone who is involved at any stage of the trial, the randomization list is generated by a person not belonging to the study team on www.randomizer.at and stored off site. Directly after inclusion of the patient the principal investigator (PI) seeks information about group allocation through a phone call or an e-mail. As soon as a child is allocated to one of the two groups, the assessments and trainings are planned according to the assigned intervention sequence, taking into account as much as possible the families’ requests and the school schedule of the child.

The rater of the primary outcome and parts of the secondary outcomes is blinded as the performance of the child in these tests is video recorded and scored by means of these videos with the rater being unaware of the date the video has been recorded. The same applies to the statistician.

